Following screening, 60 patients presenting MRSE (assessed by a standardized questionnaire; see **Appendix 3, questionnaire 3**) under statin monotherapy (any statin, any dosage) as well as 30 patients without MRSE under statin monotherapy (paired for statin and dosage with the MRSE cohort) will be evaluated. Muscle strength and fatigability will be tested by standardized procedures before and after two months of stopping statin monotherapy. Briefly, strength of the extensors and flexors muscles of the dominant leg will be quantified with a Biodex isokinetic dynamometer available in our research centre. Forces will be tested during 3 reps at 60 and 180 deg/sec and endurance during a 15 reps test at 180 deg/sec. These tests will be preceded by a 5 reps warm-up at 60 deg/sec including one movement at maximal voluntary contraction [46]. Each maximal concentric contraction will be performed in the first 90 degrees of the knee range of motion. Patients will sit in an upright position and mechanical axis and resistance pads will be aligned according to the manufacturer's guidelines. The results will be reported in Newton-meters (Nm). Peak torque, rate of torque development and total work values will be obtained following these isometric and isokinetic measurements. These groups of muscles were selected because muscle weakness or myalgias with statins are most frequently localized in lower limbs. Handgrip strength of the dominant hand will also be tested in a static mode with a Jamar dynamometer (best of 3 repetitions). These testing procedures are well standardized, easy to perform and very reproducible, and are routinely used in the department of physical therapy at our centre. Test-retest variability for the Biodex measurements is shown to be within  $\pm 15\%$  [46], which our personal experience confirms. The primary efficacy parameter will be the percent change for these measurements from baseline to end of each phase of the study.

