**Research Proposal**

---

Subjects (see **APPENDIX 1, Table 1**) in our study were statin users and had muscle side effects (cramps, myalgia, reduced muscle endurance) evaluated with our in-house questionnaire (see **APPENDIX 3, questionnaire 3**). All subjects were in primary cardiovascular prevention. Different statins were used by different participants, the majority at low doses (the highest being 20 mg).

After statin withdrawal, all subjects reported important decreases in the level of pain experienced (**APPENDIX 1, Figure 1**), and 70% showed functional improvements in at least one Biodex measure of muscle performance (**APPENDIX 1, Figure 2**). On average, the strength of the extensor and flexor muscles increased by  $22\pm 43\%$  and  $17\pm 28\%$  respectively, power by  $28\pm 64\%$  and  $29\pm 41\%$ , and endurance by  $28\pm 57\%$  and  $20\pm 35\%$  (means $\pm$ SD). No effects were observed on blood CK and AST values (**APPENDIX 1, Table 2**).

Our preliminary results show that cessation of statin therapy increased muscle functional capacity in the majority of subjects who experienced *a priori* muscle discomfort. ***Since this condition could affect the pharmacological compliance and potentially modify the cardiovascular benefits of statins, it is imperative to better characterize this dysfunction and develop approaches to reduce its impact.***

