Participants will be required to provide informed consent, will be assured confidentiality and will be offered the possibility to withdraw from the study at any time and without justification. Premature withdrawals and their causes will be carefully documented. Subjects who withdraw before the required sample size has been attained will be replaced; those who withdraw after the required sample size has been attained will not be replaced.

**EXPECTED FINDINGS AND OUTCOMES.** *This second phase of the proposal will allow us to confirm that MRSE suffering patients may be protected against statin-induced myalgia as well as for muscle function and biological markers of muscle cell degeneration after vitamin D supplementation. In addition, these data will demonstrate a significantly improved capacity to achieve lower LDL-cholesterol levels in cardiovascular prevention while reducing the risk of muscle side-effects from statin use.*

Primary outcomes for this objective include: (1) reduced functional impact of statins on muscle strength and endurance in the vitamin D supplemented group, and (2) a greater tolerance of statin reintroduction (i.e., fewer self-reported MRSE) in the group receiving vitamin D supplementation; secondary outcomes will be (3) the normalization of muscle histological, ultrastructural, and mitochondrial (metabolic) abnormalities with vitamin D supplementation and (4) the demonstration of improved statin tolerance with vitamin D supplementation regardless of initial 25(OH)D status.

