## **5.0 STATISTICAL ANALYSES**

Although there are no published data on the loss of muscle force in humans following statin treatment, experiments using men with coronary artery disease showed that  $n = 10$  to  $20$  is sufficient to distinguish differences between groups [58]. Based on the high accuracy of the Biodex apparatus and our preliminary data, we calculate that a total of 60 MRSE suffering patients will be sufficient to demonstrate effects on muscle function by statin withdrawal or vitamin D supplementation (30 per group, one with vitamin D, the other with placebo - see APPENDIX 3 for Power Calculations). These sample sizes are similar to those producing data showing reversible myositis-myalgia in statin-treated low serum 25(OH)D patients receiving vitamin D repletion [43, 44]. For biopsies, the number of subjects in each study group was determined based on our previous work (*e.g.*, [49]), biopsy feasibility and the availability of patients from our clinic [59]. From the patient case reports documented with some of these MRSE and considering the analytical precision of the methods proposed, we are confident that we will show statistically significant differences between MRSE suffering and not suffering patients [13].

Statistical analyses will test the comparison of subgroups (with/without symptoms and with/without vitamin D repletion) on the percent change from baseline (end – baseline) of specific measurements. Changes from baseline (end – baseline) of all clinical muscle symptoms will be also analyzed. Normal distribution of fasting marker levels will be examined and, if necessary, they will be normalized by transformation prior to statistical analyses in order to reduce the skewness of their distribution. One-way ANOVA will be used to compare means of continuous variables. Differences in proportions (*e.g.* proportion of patients having increments in one or more specific markers) will be compared using either the Chi-square test, or the Fisher's exact test when appropriate. Statistical analyses will be performed using SAS (SAS Institute Inc.) and/or JMP (SAS Institute Inc.) software. All tests will be two-tailed and considered statistically significant when alpha level  $< 0.05$ .

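### The primary efficacy parameter is an unranked set of strength measures alongside symptom outcomes, every test is judged at two-sided 0.05, and no rule says which result decides

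*Protocol*

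**What the plan says.** Protocol, section 3.0, Objective #1, Functional assessment and blood samples, describes the tests. On the muscle groups: "strength of the extensors and flexors muscles of the dominant leg will be quantified with a Biodex isokinetic dynamometer". On the test conditions: "Forces will be tested during 3 reps at 60 and 180 deg/sec and endurance during a 15 reps test at 180 deg/sec". On what is derived from them: "Peak torque, rate of torque development and total work values will be obtained following these isometric and isokinetic measurements". Handgrip of the dominant hand is added. The paragraph ends: "The primary efficacy parameter will be the percent change for these measurements from baseline to end of each phase of the study". No measure is placed above another.

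The Expected findings and outcomes paragraphs add to this. Objective #1 has two primary outcomes: resolution of myalgia after stopping the statin, and reduced muscle function (strength and endurance) in patients with muscle symptoms. Objective #2 also has two. The first is "reduced functional impact of statins on muscle strength and endurance in the vitamin D supplemented group", and the second is better tolerance of the reintroduced statin, read from self-reported muscle symptoms.

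Section 5.0 compares patients with and without symptoms, and with and without vitamin D. It sets one threshold for everything: "All tests will be two-tailed and considered statistically significant when alpha level" is below 0.05. It gives no order of testing, no adjustment, and no statement of how many primary measures must succeed. As an example of a proportion to be compared between groups it mentions the "proportion of patients having increments in one or more specific markers".

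**The concern.** When several measures are all primary and each is tested at 0.05, the chance that at least one is significant by luck exceeds 0.05. How far depends on how many there are and how strongly they correlate. Nothing in the protocol says whether one significant measure is enough, or which one counts if extensors and flexors, or the two speeds, disagree. The conclusion on muscle function could then rest on whichever measure came out best. The stake is the trial's main message: that vitamin D protects muscle function when a statin is reintroduced, which section 8.0 presents as a possible new approach to treating dyslipidaemic patients.

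**Working it through.** **The plan's own figure.** Section 5.0 states 60 patients with muscle symptoms, 30 per arm. The power appendix is not in the public text, so neither the target difference, the power nor the measure used is known, and the figure cannot be reproduced.

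**Counting the measures.** The protocol gives no number, so three readings are used:
- Narrow: one value per muscle group for each of three tests (60 deg/s, 180 deg/s, endurance), plus handgrip: 2 × 3 + 1 = 7.
- Crossed: 2 muscle groups × 2 speeds × 3 parameters, plus handgrip: 2 × 2 × 3 + 1 = 13.
- Crossed, plus one endurance value per muscle group: 13 + 2 = 15.

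**Chance of at least one false positive, one comparison in one phase, no true effect.** If the m measures were independent, this is 1 − 0.95^m:
- m = 7: 1 − 0.95^7 = 0.302
- m = 13: 1 − 0.95^13 = 0.487
- m = 15: 1 − 0.95^15 = 0.537

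Measures from one leg on one machine are likely to be correlated. The protocol gives no correlation, so a range is assumed, with equally correlated normal test statistics and rejection beyond ±1.96:

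| Measures | Independent | 0.5 | 0.7 | 0.8 | 0.9 |
|---|---|---|---|---|---|
| 7 | 30% | 23% | 18% | 15% | 11% |
| 13 | 49% | 33% | 24% | 19% | 14% |
| 15 | 54% | 36% | 26% | 20% | 14% |

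The smallest entry is about twice the nominal 5%. The symptom outcome, the second contrast and the repeat over phases are not included and can only add to it.

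**What different repairs cost in power.** As an illustration only, take the preliminary extensor-strength change (mean 22%, SD 43%, 9 patients, within-patient and uncontrolled) as if it were a difference between arms. With 30 per arm, the standardised difference divided by its standard error is (22/43) / √(2/30) = 0.512 / 0.258 = 1.98. Power, by normal approximation:
- One primary measure at 0.05: Φ(1.98 − 1.96) = 51%
- First Holm step of two outcomes, at 0.025: Φ(1.98 − 2.24) = 40%
- Bonferroni over 13 measures, at 0.05/13 = 0.00385: Φ(1.98 − 2.89) = 18%

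Naming one measure therefore preserves far more power than correcting across the whole set.

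**The case against.** The strongest reply is that ranking of endpoints and multiplicity adjustment are often settled in the statistical analysis plan, which is not shown, and that the unseen power appendix may identify a single measure. This stands in part. Silence on adjustment alone would not be a finding. But the protocol is not silent: it makes a plural set primary and applies 0.05 to all tests. A later plan would have to override that text.

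A second reply is that 13 is only one reading and that 49% requires independence. Both points are right. A reader might infer a minimum of 13 measures and an even chance of a false claim; the text supports neither. The conclusion does not need them, because 7 measures at a correlation of 0.9 already give 11%.

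Two stronger readings are tempting and should be resisted.
- A reader might infer that the proportion with "proportion of patients having increments in one or more specific markers" also creates false positives, because noise alone can push one of many measures upward. The protocol gives it only as an example, does not call it primary, and does not define the markers; the same section uses the word for fasting blood levels. The proportion is also compared between groups, and noise raises it equally in both. With 30 per arm, exact calculation gives a type I error of at most 2.7% (Fisher) or about 5% (chi-square) at underlying rates from 0.5 to 0.9, falling towards zero near 1. If it were applied to strength, the risk would be a ceiling in both groups and lost power.
- A reader might infer that the preliminary result, "70% showed functional improvements in at least one Biodex measure of muscle performance", is no better than chance. The threshold for improvement is not shown. If any rise counts, noise alone over the six reported measures gives 98% if independent, 86% at a correlation of 0.5, 73% at 0.8 and 66% at 0.9. With a threshold of one standard deviation it gives 45%, 32% and 27% at correlations of 0.5, 0.8 and 0.9. The 70% lies inside that span, and there were only nine patients, so no conclusion follows either way.

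**Conclusion.** The point holds: as written, the protocol does not hold the error rate of its primary functional claim at 5%. Per comparison and phase, that rate is 11% to 30% for 7 measures and 14% to 49% for 13, with 14% to 33% for 13 measures at correlations of 0.9 to 0.5. These figures rest on an assumed count, an assumed common correlation and no true effect on any measure. The direction does not depend on them, since every case tried exceeds 5%. It must be corrected, because the trial's main conclusion depends on which measure is allowed to decide. The finding is confined to the unranked primary set and the single 0.05 threshold. It does not extend to the example proportion in section 5.0 or to the preliminary data.

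**What to change.** Before any outcome data are seen:
- Name one functional primary measure for both objectives. Dominant-leg knee-extensor strength at 60 deg/s is a candidate, because the preliminary study used that test. If the power appendix was built on another measure, use that one.
- In each objective, fix one time point and one contrast for it. In Objective #2 this could be vitamin D against placebo among patients with muscle symptoms, at the end of statin reintroduction, which matches the 30 per arm in section 5.0.
- In each objective, test this measure and the symptom or tolerance primary outcome by Holm, or in a stated fixed order, at overall two-sided 0.05. Objective #1 needs the rule as much as Objective #2, since it also has two primary outcomes.
- Make all other strength measures secondary, with estimates and confidence intervals.
- State that the proportion with a rise in one or more markers supports no primary claim, and define its markers and threshold if it is kept.

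The change is one of wording. It has two costs. A result on a non-primary measure becomes supportive only. Holm also lowers power for the first test, from 51% to 40% in the illustration above; a fixed order avoids that for the outcome tested first, but the second can be tested only if the first succeeds.

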**Research Proposal**

---

Subjects (see **APPENDIX 1, Table 1**) in our study were statin users and had muscle side effects (cramps, myalgia, reduced muscle endurance) evaluated with our in-house questionnaire (see **APPENDIX 3, questionnaire 3**). All subjects were in primary cardiovascular prevention. Different statins were used by different participants, the majority at low doses (the highest being 20 mg).

After statin withdrawal, all subjects reported important decreases in the level of pain experienced (**APPENDIX 1, Figure 1**), and 70% showed functional improvements in at least one Biodex measure of muscle performance (**APPENDIX 1, Figure 2**). On average, the strength of the extensor and flexor muscles increased by  $22\pm 43\%$  and  $17\pm 28\%$  respectively, power by  $28\pm 64\%$  and  $29\pm 41\%$ , and endurance by  $28\pm 57\%$  and  $20\pm 35\%$  (means $\pm$ SD). No effects were observed on blood CK and AST values (**APPENDIX 1, Table 2**).

Our preliminary results show that cessation of statin therapy increased muscle functional capacity in the majority of subjects who experienced *a priori* muscle discomfort. ***Since this condition could affect the pharmacological compliance and potentially modify the cardiovascular benefits of statins, it is imperative to better characterize this dysfunction and develop approaches to reduce its impact.***

### **Histological assessment of skeletal muscle**

For a subset of 30 of the patients in the study (20 presenting MRSE and 10 without MRSE), percutaneous needle biopsies of the *vastus lateralis* muscle will be performed, before and after two months of discontinuation of statin monotherapy, in our outpatient surgical center. [name] (Laval University), who has performed this procedure literally hundreds of times over the years, will be responsible for biopsies (see **letter of collaboration**). This technique is relatively painless (especially in patients with normal CK), well tolerated, can be performed within 20 minutes, and is routinely used in our laboratory for repeated measures over time [49]. A control group of 10 statin-naïve patients will have the same muscle functional testing and venous punctures collection at the start of the study and two months later; 5 of these will also have muscle biopsies.

Muscle biopsies will be analysed histologically with standard muscle stains and also frozen for future analyses using methods routinely used in our laboratory (e.g., [49] and **APPENDIX 4, publications 2, 3 and 4**). Mitochondrial-like myopathy features associated with statin-myopathy (lipid droplet accumulation in type 1 fibers by oil red O staining, ragged red fibers, cytochrome oxidase-negative myofibers, mitochondrial protein profiling), myocyte fiber morphometry (size, type) and degenerating/regenerating fiber distribution (indicated by central nuclei stained with hematoxylin-eosin) will be assessed ([50, 51], and **APPENDIX 4, publications 2 and 3**). Enzyme activities and protein levels relating to energy metabolism (citrate synthase, cytochrome-c oxidase, hydroxyacyl-CoA dehydrogenase) or proteolysis (atrogin, Murf) will also be measured (see [52] and **APPENDIX 4, publications 2 and 3**). Mitochondrial protein expression profile for PPAR- $\gamma$  coactivator-1 $\alpha$  (PGC-1 $\alpha$ ) and downstream target proteins, protein import machinery components (Hsp60, Tom40 and Tom22), fusion proteins (mitofusin 2 (Mfn2) and optic atrophy 1 (Opa1)), fission protein (Drp1), apoptosis related proteins (Bax and Bcl-2), and autophagy proteins (Beclin 1 and light chain 3 (LC3-II)) will be assessed using previously established Western blotting methods (**APPENDIX 4, publication 4**) in collaboration with [name] (York University; see **letter of collaboration**). The secondary efficacy parameters will be the qualitative or quantitative changes observed from baseline to end of each phase of the study.

**EXPECTED FINDINGS AND OUTCOMES.** *This first phase of the proposal will allow us to confirm the loss of muscle functional capacity, as well as the nature of skeletal muscle structural and biochemical changes and tissue damage in those patients presenting MRSE.*

Primary outcomes for this objective include: (1) the demonstration of myalgia resolving with statin cessation and (2) the demonstration of reduced muscle function (strength and endurance) in

**Research Proposal**

patients suffering from statin-related myalgia; a secondary outcome will be (3) the assessment of muscle histological, ultrastructural or metabolic changes potentially relating to expression of MRSE (in particular, muscle mitochondrial rearrangements are predicted).

**OBJECTIVE #2:** *To assess the usefulness of vitamin D supplementation in improving muscle function and structure and reducing muscle-related side effects.*

**Trial design**

This study will use an outpatient, randomized, double-blind (participants, research nurse, coordinator, investigators, interviewers, statisticians, treating physicians), prospective trial design with stratification on MRSE status, plasma 25(OH)D status, age and sex, with repeated measures at 4 weeks post-randomization and at up to 8 weeks post-statin reintroduction. This is diagrammed in Figure 1. Participants (from Objective #1) will first be divided into 2 groups according to their MRSE status: statin taking with MRSE and statin taking without MRSE. Participants in each group will then be randomly assigned to either the experimental (vitamin D) or the control (placebo) arm. The placebo will as closely as possible match the color, taste and consistency to the vitamin D administered in the experimental group.

The research coordinator and other members of the research team will be responsible for recruitment, testing, data collection and follow-up. Allocation of participants to treatment arms and statin, vitamin D and placebo supply and distribution will be under the responsibility of the Department of Pharmacy of the CHUL (see budget supporting document).

Vitamin D status will not be used to select subjects for initial (Objective #1) enrolment in the study, but will be used to stratify subjects in the RCT. Subject vitamin D status will be defined using cut-offs discussed in a recent Statistics Canada Health Report [45].

In the experimental group (n=45; 30 with MRSE under statin monotherapy, 15 without MRSE under statin monotherapy from objective #1), statins will be reintroduced following one month of oral vitamin D supplementation (Vitamin D3 [cholecalciferol], Laboratoire Riva Inc., Blainville, Québec; 4 x 10,000 IU/week, 40,000 IU/week total). This falls within the range of average daily dosage used in the studies of Lee *et al.* [44] and Ahmed *et al.* [43] that showed relief from myalgia and allowed statin reintroduction in patients with low serum 25(OH)D levels. This also falls within the generally acceptable upper limit of daily vitamin D intake, the “no observed adverse event level” being 10,000 IU per day, and well below the “lowest observed adverse event level” of 40,000 IU per day (as discussed in [45]). Patients will be rechallenged with the same statin and at the same dose they were taking at the onset of objective #1. Patients will continue to supplement with vitamin D during the statin rechallenge period, which will last for a maximum of 2 months. The patients may request at any time over this period the cessation of statin therapy if they consider any reappearance of MRSE to be too severe to continue. Based on the clinical experience of [name] (co-PI), patients rarely develop muscle symptoms in less than 2 weeks following statin introduction.

In the control group (n=45; 30 with MRSE under statin monotherapy, 15 without MRSE from objective #1), no vitamin D supplementation will take place prior to statin reintroduction, subjects receiving instead a placebo provided by the pharmacy service of the CHUL. Placebo supplementation will also continue following statin reintroduction (1 month after the start of the RCT). Readers are referred to figure 1 and table 1 for more details on patient assignment.

Participants will be asked by the study coordinator, by phone, a few days before their visits at 4 weeks after randomization and at end-of-trial, to bring their bottles of capsules for their visit to the CHUL. The pharmacy will then check their apparent compliance by counting the remaining capsules and surveying the participants on their supplementation practices. A compliance rate of at least 80% will be required for successful outcome in the trial.

The changes in 25-OH vitamin D, calcium, phosphate, alkaline phosphatase, and parathyroid hormone, from baseline to end of each phase of study will be studied in all patients to evaluate the

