**Research Proposal**

---

prescribed chronic medications are compliant [9]. Statins are no exception to this observation. The proportion of patients in the province of Quebec who were 80% adherent over 2 years of statin treatment was less than 60% [10]. Of 100 patients starting statins for the primary prevention of coronary events, 44 will have discontinued therapy before any clinical benefit can be expected [11]. We suspect that statin-induced MRSE contribute significantly to this phenomenon, although this has not been studied.

***Statin-induced MRSE remain an underappreciated phenomenon, and very little is known on their effects on patient compliance or on how to prevent or reduce these symptoms.***

**Statins, muscle strength, and exercise performance.** Very few data are available on the effects of statins on muscle function. The authors of a recent review [12] examined published reports on the effects of statins on skeletal muscle strength and exercise performance and identified only 6 studies with data on the effects of statins on muscle strength, and 9 with data on exercise performance. Their main conclusions were that “there is insufficient data to determine if statins affect muscle strength and exercise performance” and that “there is suggestive evidence that these drugs may reduce muscle strength in older patients and alter energy metabolism during aerobic exercise”. The paucity of data on these issues clearly warrants further studies. ***To our knowledge, no study has systematically examined the impact of statin-induced myalgia on muscle strength and endurance.***

Complicating matters further, a number of major confounders and technical problems are found in the few studies examining statin effects on muscle function. First, the characteristics of subjects under statins are often incomplete. For example, most of these studies do not distinguish between patients with or without statin-related myalgia. Also, in many of the studies, the precise methods used to assess muscle function are either poorly described, or are subject to significant error and are inappropriate for small group studies.

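### Compliance is checked only for the vitamin D/placebo capsules; intake of the rechallenged statin is not verified, so silent skipping can pass as tolerance

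*Protocol*

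**What the plan says.** Protocol section 3.0, Objective #2, Trial design, describes one compliance procedure. Before the visits at 4 weeks after randomisation and at end of trial, participants are asked "to bring their bottles of capsules for their visit to the CHUL". Then: "The pharmacy will then check their apparent compliance by counting the remaining capsules and surveying the participants on their supplementation practices". The next sentence sets a threshold without naming a product: "A compliance rate of at least 80% will be required for successful outcome in the trial".

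The same section describes the exposure that Objective #2 depends on: "Patients will be rechallenged with the same statin and at the same dose they were taking at the onset of objective #1". Rechallenge lasts at most 2 months, and patients may ask to stop the statin if returning symptoms are too severe. On logistics, "statin, vitamin D and placebo supply and distribution will be under the responsibility of the Department of Pharmacy" of the hospital.

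The two primary outcomes (Objective #2, Expected findings and outcomes) are a smaller functional impact of statins on strength and endurance, and better tolerance of reintroduction, which is defined by self-reported MRSE. Section 2.0 notes that fewer than 60% of Quebec statin patients were 80% adherent over 2 years. It comments "We suspect that statin-induced MRSE contribute significantly to this phenomenon", adding that this has not been studied.

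**The concern.** Both primary outcomes of Objective #2 presuppose that the statin is taken during rechallenge. If it is not, the absence of symptoms or of strength loss says nothing about tolerance. The described check covers another product, so at the end of the trial a patient who tolerated the statin cannot be told apart from one who quietly took little of it.

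The 60 MRSE patients are selected because they had symptoms on this drug, and the protocol itself suspects such symptoms of driving non-adherence. Skipping may therefore be a consequence of the outcome. If vitamin D protects, fewer patients on that arm have a reason to skip, so statin exposure would differ between arms in the direction that hides the benefit. Intake data that are not collected cannot be recovered by a later analysis plan.

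**Working it through.** The protocol states no figure on this point, so there is none to reproduce. The check has two parts.

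**1. What could record statin intake during rechallenge**

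- *Capsule count and survey, week 4.* Statins return after one month of supplement, and the week-4 tests are taken immediately before reintroduction. This check cannot measure rechallenge intake.
- *Capsule count and survey, end of trial.* The timing is right, but the survey concerns supplementation. The word capsules is not defined; vitamin D/placebo is the natural reading.
- *Declared cessation.* Testing follows within 1 week of stopping for important MRSE. Undeclared skipping triggers nothing.
- *Phone interviews every 2 weeks.* They assess adverse events. No question on statin intake is described, nor any link to the tolerance outcome.
- *MRSE questionnaire.* The rechallenge version is given at the end of reintroduction, when symptoms may have faded after skipping.
- *Lipids (section 4.0).* LDL-cholesterol is measured at the end of each phase, under statin efficacy. It could reveal gross non-intake but is not assigned that use.

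None of these verifies statin intake directly.

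**2. How much it could matter (illustration on assumed rates)**

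Inputs from section 5.0: 30 MRSE patients per arm, two-sided 0.05, Fisher's exact test among the tests named for proportions. Assumptions, none of them in the protocol: tolerance is analysed as recurrence yes/no; true recurrence is p = 0.75 on placebo and q = 0.35 on vitamin D; and a share s of patients who would have MRSE skip enough statin to report none.

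Observed rates are p(1 − s) and q(1 − s), so the difference is (p − q)(1 − s). Power is the sum, over all pairs of counts (a, b) with Fisher p ≤ 0.05, of Bin(a; 30, p(1 − s)) × Bin(b; 30, q(1 − s)).

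| s | Placebo | Vitamin D | Difference | Power |
|---|---|---|---|---|
| 0 | 0.750 | 0.350 | 0.400 | 0.84 |
| 0.05 | 0.7125 | 0.3325 | 0.380 | 0.79 |
| 0.10 | 0.675 | 0.315 | 0.360 | 0.74 |
| 0.30 | 0.525 | 0.245 | 0.280 | 0.51 |

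At s = 0.10 the expected number of hidden recurrences is 30 × 0.75 × 0.10 = 2.25 on placebo and 30 × 0.35 × 0.10 = 1.05 on vitamin D, about three patients in all. An equal tendency to skip once symptomatic already gives more skipping on placebo.

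Other assumed rates, using the normal approximation for two proportions, show the same pattern. For 80% versus 40%, power is 0.91, 0.82, 0.71 and 0.49 at s = 0, 0.10, 0.20 and 0.40. For 70% versus 35% it is 0.79, 0.70, 0.60 and 0.42.

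**The case against.** The strongest reply is that tolerance is defined by self-reported MRSE, not by staying on the drug. A patient who skips because of symptoms has had the outcome, and either the two-weekly calls or the end questionnaire may record it. Patients can ask to stop at any time, which lessens the motive to skip silently, and a declared stop leads to prompt testing. Adherence over 2 years in routine care is a weak guide to at most 2 months under pharmacy supply and regular calls. All of this stands, and it makes misclassification conditional: symptoms must return, the patient must skip silently, the symptoms must fade, and neither the calls nor the questionnaire must pick them up.

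Three stronger readings are tempting and not supported:

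- *A reader might infer that a patient who skips is scored as tolerating the statin.* No rule says so.
- *A reader might infer that nothing planned could reveal a difference in intake.* End-of-phase lipids could, if it were large.
- *A reader might infer a near-total loss of power.* Confining the skipping to placebo gives 0.675 versus 0.350 (power 0.64) at s = 0.10 and 0.525 versus 0.350 (power 0.20) at s = 0.30. The protocol suggests no reason why symptomatic patients on vitamin D, in a double-blind comparison, would never skip.

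Nor does the gap make a positive result suspect by this route: if skipping is commoner on placebo, a finding in favour of vitamin D would be conservative. Finally, Figure 1 and the Appendix 3 questionnaires are not shown, so they may already ask about statin intake.

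What remains is that no visible text plans to verify intake of the drug under challenge, and the indirect safeguards are not set up to do it.

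**Conclusion.** The point holds as a gap in data collection. The only compliance check in the visible protocol covers the supplement; statin intake during rechallenge is unverified, and silent skipping can pass as tolerance. If commoner on placebo, it would pull both the tolerance and the strength comparisons toward no effect, and a null result could not be separated from low statin exposure. The size is unknown. The illustration gives a loss of about 10 percentage points of power at 10% hidden skipping (84% to 74%) and about 33 at 30% (84% to 51%). Both rest on assumed recurrence and skipping rates, a yes/no outcome and complete loss of the symptom report. The change is worth making because it is cheap and the data cannot be obtained afterwards.

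**What to change.** Four additions to contacts and data already planned:

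- At the end-of-trial pharmacy check, have participants bring the statin bottle as well. Count tablets returned against tablets dispensed since reintroduction, and extend the survey to skipped or reduced statin doses, with reasons.
- Add one question on statin intake to each two-weekly call made during rechallenge.
- Prespecify that undeclared interruption or reduction of the statin because of muscle symptoms counts as an MRSE/intolerance event in the tolerance outcome.
- Report the LDL-cholesterol change over rechallenge by arm as supportive evidence of statin intake.

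The protocol should also say which product the 80% compliance threshold refers to.

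The cost is slightly more pharmacy and interview work, with no extra visit. Tablet counts remain an imperfect measure of intake, since a returned bottle does not prove that the missing tablets were swallowed; the LDL-cholesterol comparison partly offsets this.
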